### Study objectives

In the project “DASI” (acronym for ‘Digital assistierte Informationserfassung vor der Sprechstunde’; i.e. ‘Digitally supported system to obtain patient’s medical history before consultation’), we aim at piloting and evaluating a software application (app) developed for a structured symptom-oriented medical history taking among patients with acute medical complaints in general practice. While accuracy of obtained information and usability has been studied in another project [19], this study firstly addresses whether an app designed to obtain medical history before consultations in addition to regular medical history taking can improve diagnostic accuracy. Secondary, we aim to evaluate whether the use of the app prior to medical consultation increases patient satisfaction and reduces physicians’ perceived diagnostic uncertainty.

Within the framework of explorative data analysis (machine learning and data mining), complex prediction models are modeled based on the medical history data. The data is used to illustrate the potential use and opportunities of the software application for intelligent patient management, diagnostic and scientific purposes.

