#### Big Data objectives

At the time of the final evaluation, there is an extensive standardized dataset of approximately 1,000 patients. A partial data set is to be evaluated in the context of a machine learning / data mining procedure. The aim is (a) to assess the usability of the data for further purposes (intelligent patient management and diagnostics) and to demonstrate this in a use case (e.g. predicting hospital admission), and (b) to characterize the usage process and to identify possibilities for improvement of the user interface.

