#### Intervention group

In the intervention group, the participant then receives a tablet with the app installed. The participant completes the digital medical history in the waiting area. At the end of the survey, the app generates a report from the participants’ responses, which is subsequently transferred to the EMR via a scanned QR-code. This report is available to the physician before the consultation. No data remains stored on the device itself.

When they are next in line, the participant goes to the doctor’s office for consultation. After the consultation, both the participant and the physician are asked to fill out a short questionnaire. The participant will be asked questions about their satisfaction with the consultation (EUROPEP) and about communication (PSQ) and socio-demographic questions. These questions will be presented on the study tablets using the survey software Limesurvey. Subsequently, each participating patient receives a compensation of EUR 15.

The physician is asked to document the ICD-10-GM code (WHO Version 2019) of the (preliminary) diagnosis, to answer questions about their experience of uncertainty regarding this diagnosis and questions matching those that the participant is asked about communication. Additionally, we will collect data regarding the physicians’ specializations and experience (i.e. year of approbation and year of the first specialist examination).

After 14 to 21 days, we conduct a short follow-up to ask participants about their further treatment (e.g. by their family doctor, specialist treatment and hospital admissions). Participants may answer these questions via an online questionnaire (accessed using a personalized link which is sent per e-mail or text message) or by telephone (interview conducted by a study nurse).

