### Statistical design

We will use descriptive statistics to analyze patient characteristics (i.e. demographics, medical complaints) of intervention and control group. Furthermore, the groups will be compared according to characteristics of the recruitment centers.

The primary outcome “diagnostic accuracy” defines the agreement of a given diagnosis with the determined correct diagnosis. The primary evaluations of the binary endpoint of an adequate diagnosis are performed by a generalized linear mixed-effects model (hierarchical or multilevel model) with logit link function. The group (intervention versus control) and the respective out-of-hours practice are included as fixed effects, and the time period (cluster) as a random effect. The random effect is assumed to be normally distributed on the logit scale. The expected value is 0. The variance is unknown and estimated from the data. The odds ratio for the intervention effect will be reported together with its 95% confidence interval and a p-value for the null hypothesis that the intervention does not increase the diagnostic accuracy. Subgroup analyses will explore whether practice characteristics such as experience or specialization of the physicians have an influence on the strength of the intervention effect. This will be done by extending the model described above. Specifically, the respective practice characteristic as well as its interaction with the intervention effect will be included in the hierarchical model. With regard to the secondary endpoints, the individual items of the respective questionnaires are first presented within the framework of descriptive statistics (median, max, min, percentiles). Differences between the intervention and control group are analyzed for each item of the questionnaires using non-parametric methods. Except for the primary endpoints all endpoints are considered exploratory. Therefore, p-values will not be adjusted for multiplicity. Further explorative evaluations will be conducted using machine learning and data mining procedures: methods that are known to work well with a medium sample size will be used for classifications. These methods should have the potential to capture the structure of the underlying associations. We assume that some effects of inquired symptoms on the suspicion of disease severity are additive and individually assessable while others are more likely to conform to a relation like “at least k of n criteria have to be met and none of the following contra-indications” and are more specific to single diseases. We use elastic nets for classifications, because they perform well with the first class of symptom effects even when the number of inquired symptoms is larger than the number of patients. We will also use random forests, because they structurally have some similarity to decision tree like associations that can handle the second class of symptoms. We will utilize the results from these methods to artificially expand the data set for (or to pre-train) more flexible algorithms, such as support vector machines and artificial neural networks. These will then be used to search for more complicated associations. Medical history information, demographic information, treatment information (e.g. diagnosis, examination findings), and event-sourcing information (tracking of the app-usage of individual patients, e.g. time needed to complete) will be used as input variables. In addition, cluster, association and regression analyses will be performed. Results will be visualized and interpreted. Test data from the overall evaluation will be used to determine sensitivity, specificity, and accuracy of prediction models.

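### The exploratory prediction models take the physician's diagnosis and examination findings as inputs, so their reported accuracy cannot be attributed to the app-collected history

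*Protocol article*

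**What the plan says.** Three sections of the protocol article describe this work.

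- **Study objectives** gives the basis and the purpose. In the exploratory part, "complex prediction models are modeled based on the medical history data", and "The data is used to illustrate the potential use and opportunities of the software application for intelligent patient management, diagnostic and scientific purposes".
- **Big Data objectives** sets two aims. Aim (a) is to judge whether the data can serve patient management and diagnostics, and "to demonstrate this in a use case (e.g. predicting hospital admission"). Aim (b) is "to characterize the usage process and to identify possibilities for improvement of the user interface".
- **Statistical design** fixes the inputs in a single list: medical history, demographics, "treatment information (e.g. diagnosis, examination findings), and event-sourcing information", the last being the tracking of app use. It then states how performance is judged: "Test data from the overall evaluation will be used to determine sensitivity, specificity, and accuracy of prediction models".

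The section Intervention group shows where the diagnosis comes from: "The physician is asked to document the ICD-10-GM code (WHO Version 2019) of the (preliminary) diagnosis". The same step applies in the control group. The whole programme is labelled exploratory.

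**The concern.** The objective is a statement about the app: what can be done with the history it collects. The input list includes what the physician concluded and found at the visit. If a model has seen both, its sensitivity, specificity and accuracy describe the two sources together. A good figure could then be read as evidence for the app when the app answers had added little, and nothing in the reported figure would reveal this.

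There are two further consequences. For patient management before the visit, the physician-derived inputs do not yet exist, so the reported performance would not be achievable in that use. And if the target is the diagnosis, or something decided at the visit, an input that carries the same information makes the prediction circular.

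Limiting the analysis to intervention weeks would not help. The diagnosis and examination findings arise at the consultation in both groups, and in intervention weeks the diagnosis may already reflect the app report.

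**Working it through.** **Plan's own figure.** The protocol gives no performance figure for the prediction models, so there is none to reproduce. Its sample-size figures do not bear on this point.

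**Step 1: when each variable comes into being.**

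| Variable | Role | Available | Section |
|---|---|---|---|
| App answers, app-usage data | input | before the consultation in intervention weeks, after it in control weeks | Intervention group; Control group |
| Demographics | input | not produced by the consultation | Statistical design |
| Diagnosis | input | at or after the consultation, from the physician | Intervention group |
| Examination findings | input | at the consultation, from the physician | Statistical design |
| Hospital admission | example target | follow-up at 14 to 21 days | Intervention group; Big Data objectives |

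**Step 2: purpose against inputs.** Study objectives rests the models on the medical history data. Statistical design states that a longer list will be used, and two of its named items come from the physician. The second statement goes beyond the first, and the reported performance follows the second.

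**Step 3: can the combined figure reveal the app's part?** This step uses assumed values, because the protocol gives none. Let H be a score from the app history and D a score from the physician's diagnosis and findings, both standard normal with correlation ρ, and let

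logit P(target = 1) = −2.2 + b_H·H + b_D·D.

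Each row is a simulation of 200,000 records, with target prevalence between 13% and 21%. The summary is the area under the ROC curve (AUC), which collects sensitivity and specificity over all cut-offs.

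| ρ | b_H | b_D | App only | Physician only | Both |
|---|---|---|---|---|---|
| 0.3 | 1 | 0 | 0.744 | 0.575 | 0.744 |
| 0.3 | 1 | 0.5 | 0.766 | 0.688 | 0.788 |
| 0.3 | 1 | 1 | 0.772 | 0.770 | 0.836 |
| 0.3 | 0.5 | 1.5 | 0.694 | 0.832 | 0.846 |
| 0.3 | 0.2 | 2 | 0.644 | 0.875 | 0.876 |
| 0.6 | 1 | 0 | 0.750 | 0.652 | 0.750 |
| 0.6 | 1 | 0.5 | 0.791 | 0.745 | 0.803 |
| 0.6 | 1 | 1 | 0.816 | 0.816 | 0.854 |
| 0.6 | 0.5 | 1.5 | 0.774 | 0.850 | 0.859 |
| 0.6 | 0.2 | 2 | 0.749 | 0.880 | 0.881 |

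**Step 4: reading the table.**

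- Where b_D = 0, the physician inputs add nothing: 0.744 − 0.744 = 0 and 0.750 − 0.750 = 0.
- Where the physician score dominates, the app adds almost nothing to it: 0.876 − 0.875 = 0.001 and 0.881 − 0.880 = 0.001.
- Two combined values that are nearly equal, 0.846 and 0.854 (difference 0.008), go with app-only values of 0.694 and 0.816 (difference 0.122).

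The combined figure therefore does not identify the app's contribution. A separate app-only fit does.

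**The case against.** The case against has four parts.

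1. *The list is pooled.* It serves a whole programme, including the description of app use, on part of the data set. Nothing says that every model uses every variable, and the reasons given for elastic nets and random forests speak of symptom effects. This stands as a reason not to assume that every model will be affected. It does not remove the problem, because the list is stated without division and aim (a) carries no restriction.

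2. *Predictors per model belong in the analysis plan.* An article may leave that detail out, and its absence alone would be no finding. Here, however, the article makes two statements that do not agree, and the longer list is affirmed. Saying that a model is based on history need not mean on history alone, but then its accuracy is not evidence about the history.

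3. *Prediction before the visit is not the only stated use.* This is correct. Admissions are collected at follow-up, so a model of later admission that uses the diagnosis can be a legitimate post-consultation model. A blanket ban on the diagnosis as an input would go too far.

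4. *The size is unknown.* This is also correct. A reader might infer that the reported accuracy would be mostly the physician's and would say little about the app. The documents do not support that. In another assumed setting, an independent consultation flag with 98% specificity and 50% or 70% sensitivity raises an app-only AUC of 0.60 to 0.79 or 0.87, and one of 0.70 to 0.84 or 0.90. The app's part of the gain over 0.5 is then 0.10/0.29 = 34% or 0.10/0.37 = 27% in the first case, and 0.20/0.34 = 59% or 0.20/0.40 = 50% in the second. The answer follows from the assumption. That these values do not change with the admission rate is a property of the AUC and no support for them.

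**Conclusion.** The point holds in a limited form. The input list as written includes variables that arise only at or after the consultation, while the stated basis is the medical history data and the stated purpose is to show the app's potential. Performance from models that follow the list cannot be attributed to the app-collected history and does not apply to patient management before the visit.

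The physician's share cannot be sized from the protocol; under the assumed effects above it ranges from nil to nearly all. The conclusion rests on the order of events and on the stated input list, not on any of the simulated values.

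It concerns a named but exploratory objective. The primary and secondary outcomes, the sample size and the comparison of the groups are not affected. The change is worth making, and it can be made at any time before the models are fitted.

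**What to change.** In Statistical design, replace the single input list by two sets and one rule.

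- **App-only set:** app answers, demographics and app-usage data. Any claim about the app or about patient management before the visit rests on these models alone. Since control patients complete the app after the encounter, the report should say which group's records a pre-visit claim uses.
- **Post-consultation set:** the app-only set plus diagnosis, examination findings or treatment information. These models are reported separately, labelled as post-consultation, and shown as an increment over the app-only model on the same test data.
- **Rule on targets:** no input may be, or directly encode, the target. Examples are the diagnosis when diagnosis is predicted, or a referral decision when admission is predicted. Using the diagnosis to predict later admission remains possible in the post-consultation set.

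The cost is a paragraph of wording and one extra model fit on data already collected. The headline accuracy may look less favourable.

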
## Discussion

There have been several attempts to develop and implement digital tools as well as paper-based questionnaires to obtain information on health concerns from patients before their encounter. While many aim to improve quality of medical care, ease documentation and enhance work efficiency, these effects have hardly been studied [18]. The purpose of this study is to generate evidence on the effect of an app for medical history taking in urgent care practices in Germany using a rigorous study design. In these urgent care practices, physicians with various specialist backgrounds have to assess complaints they normally do not see in their daily practice. The app provides them with a structured medical history that might prevent them from making diagnostic errors which might lead to insufficient and ineffective care.

Along the project, we will also gain experience on the implementation process and potential difficulties, e.g. with the technical infrastructure or users. This is important seeing that in Germany the level of digitization is low in the healthcare sector, both compared internationally and with other sectors within Germany. While physicians in Germany are increasingly positive about opportunities to improve medical care through the greater use of digital technologies [28], the difficulty of proving benefits and the lack of interoperability are considered to be major obstacles [29]. Regarding the latter aspect, it is a major challenge to make the information transferred into patients’ EMR to be of use in the long term. Up to now, it remains on the information system of the physicians on duty but cannot be exchanged with other systems or transferred to the not-yet-used individual electronic patient file. As a step towards rendering the data interchangeable we aim at developing and publishing an open digital format for symptom-oriented health inventory data.

As for limitations, we face several challenges that might introduce bias: Data collection takes place during COVID-19 pandemic with altered contact patterns in medical care. Patients with signs of a respiratory infection, for example, are sometimes not allowed to enter the waiting areas and might be underrepresented in this study. Even though elderly people are increasingly participating in the digital world [30], their usage behavior differs from that of younger people [31]. Elderly people might be less inclined to take part in a study with a digital intervention; their complaints, diagnoses and treatment courses might be underrepresented in the study. Patients with a private health insurance are less likely to seek medical care in the out-of-hour practices. Furthermore, patients with limited German-language proficiency cannot take part in this study as we focus on German speaking patients. Of note, many patients with limited German language proficiency are treated in these practices. As professional interpreter are not regularly covered through statutory health insurance and only a minority of physicians in Germany offer consultations in languages other than German or English [32], further studies should be considered to investigate the benefits for migrant and refugee patients with limited German language skills.

## Data Availability

Not applicable.

## List of abbreviations

App: software application
CRT: cluster-randomized trial
EMR: Electronic medical records
EUROPEP: European Project on Patient Evaluation of General Practice Care Questionnaire
DASI: Digital assistierte Informationserfassung vor der Sprechstunde (Digitally supported system to obtain patient’s medical history before consultation)
G-BA: Gemeinsamer Bundesausschuss (Federal Joint Committee)
ICC: Intra class correlation
ICD-10-GM: 10th revision of the International Statistical Classification of Diseases and Related Health Problems, German modification
ICH-GCP: International Conference on Harmonization Good Clinical Practice
ID: Identification number
KV: Kassenärztliche Vereinigung (Association of Statutory Health Insurance Physicians)
KVN: Kassenärztliche Vereinigung Niedersachsen (Association of Statutory Health Insurance Physicians of Lower Saxony)
PSQ: Patient Satisfaction Questionnaire
WHO: World Health Organization
